## Abstract

**Background:**

In sub-Saharan Africa (SSA) there are strong arguments for the provision of integrated sexual and reproductive health (SRH) and HIV services. Most HIV transmissions are sexually transmitted or associated with pregnancy, childbirth, and breastfeeding. Many of the behaviours that prevent HIV transmission also prevent sexually transmitted infections and unintended pregnancies. There is potential for integration to increase the coverage of HIV services, as individuals who use SRH services can benefit from HIV services and vice-versa, as well as increase cost-savings. However, there is a dearth of empirical evidence on effective models for integrating HIV/SRH services. The need for robust evidence led a consortium of three organizations – International Planned Parenthood Federation, Population Council and the London School of Hygiene & Tropical Medicine – to design/implement the Integra Initiative. Integra seeks to generate rigorous evidence on the feasibility, effectiveness, cost and impact of different models for delivering integrated HIV/SRH services in high and medium HIV prevalence settings in SSA.

**Methods/design:**

A quasi-experimental study will be conducted in government clinics in Kenya and Swaziland – assigned into intervention/comparison groups. Two models of service delivery are investigated: integrating HIV care/treatment into 1) family planning and 2) postnatal care. A full economic-costing will be used to assess the costs of different components of service provision, and the determinants of variations in unit costs across facilities/service models. Health facility assessments will be conducted at four time-periods to track changes in quality of care and utilization over time. A two-year cohort study of family planning/postnatal clients will assess the effect of integration on individual outcomes, including use of SRH services, HIV status (known/unknown) and pregnancy (planned/unintended). Household surveys within some of the study facilities’ catchment areas will be conducted to profile users/non-users of integrated services and demand/receipt of integrated services, before-and-after the intervention. Qualitative research will be conducted to complement the quantitative component at different time points. Integra takes an embedded ‘programme science’ approach to maximize the uptake of findings into policy/practice.

**Discussion:**

Integra addresses existing evidence gaps in the integration evaluation literature, building on the limited evidence from SSA and the expertise of its research partners.

**Trial registration:**

Current Controlled Trials NCT01694862

## Background

There are many well-established reasons that support the rationale for integrating or linking sexual and reproductive health (SRH) and HIV services in developing countries with generalized HIV epidemics – primarily in sub-Saharan Africa. Most HIV transmissions in these countries are sexually transmitted or associated with pregnancy, childbirth and breastfeeding. Many of the behaviours that prevent HIV transmission also prevent sexually transmitted infections (STIs) and some prevent unintended pregnancies. Individuals who use SRH services often benefit from HIV services, and vice versa, and so by integrating services, there is the potential to increase the coverage of both HIV and SRH services. There are an estimated 34 million people living with HIV worldwide at the end of 2010, up 17% from 2001 [1], and around two thirds of people living with HIV are found in sub-Saharan Africa. Globally, almost 90 million women have an unintended pregnancy each year largely due to an unmet need for family planning (FP) [2]. Findings from several studies in countries south of the Sahara have also suggested that rates of unintended pregnancies among HIV-infected women are high ranging from 51% to 91% [3-5][6]. There is a clear need to respond to the sexual and reproductive health needs of people living with HIV.

Over the past decade, a number of international statements, position papers and advocacy efforts have indicated the commitment of the international community to intensifying linkages between SRH and HIV, at both policy and health service delivery levels [7,8]. In Africa, the Maputo Plan of Action affirmed the need to act [9]. The 2005 interagency document developed by WHO/UNFPA/UNAIDS/IPPF and entitled *“Sexual and Reproductive Health and HIV, A Framework for Priority Linkages”*[10], outlined some of the ‘expected’ benefits, including improved access and efficiency of services and better health outcomes, and recognized the imperative for improving the evidence-base in order to ascertain the magnitude of these benefits. A call echoed at an international conference organized by the Bill and Melinda Gates Foundation (BMGF) in Ethiopia, entitled *“Linking Sexual and Reproductive Health, Family Planning and HIV”*[11].

In addition to these political statements and calls for evidence, four comprehensive reviews of integration literature have surveyed existing evidence. They found a range of potential benefits of integrating reproductive health and HIV services, including improvements in service utilization (such as increase in uptake of HIV testing and contraceptive use), quality of services and client satisfaction, but acknowledged many gaps in the evidence, especially for impact of integration on health outcomes and costs [12-15]. The reviews also highlight a wide range of challenges associated with integration, including provider overload and limited time, poor or insufficient provider training and motivation, and stock-outs of essential drugs and supplies.

There are a limited number of evaluative studies for integrating HIV services with components of SRH services, mostly from southern and eastern Africa where HIV prevalence is highest. Early studies on integration in sub-Saharan Africa highlighted the complexity of ensuring that the service structures, funding and commodity flows adequately supported the provision of integrated services, and found mixed evidence of clear benefits in terms of the new uptake of services or the better use of resources [16,17]. Two more recent studies from South Africa and Kenya suggest more positive results. Using quasi-experimental designs to evaluate models for integrating HIV services (STI/HIV counseling and risk assessment, HIV testing) into services for FP clients, both studies found that integration led to an increased proportion of providers discussing and offering HIV counseling and testing during FP consultations, and increases in the quality of care. Both studies also found that integrating STI/HIV counseling and offering HIV counseling and testing was feasible and acceptable to FP clients and providers [18,19]. Two other studies, in Kenya and Swaziland, evaluated models for linking and strengthening HIV screening and management and postpartum family-planning into services for postnatal clients and their newborns. Both found significant improvements in process outcomes, including uptake and quality of services and confirmed that integrated services are feasible and acceptable to both postpartum women and health care providers [20-22]. However, none of the above studies in Kenya, South Africa or Swaziland specifically focused on measuring the benefits of integrated HIV and SRH services; nor included comparison facilities nor assessed the communities’ response to these services. These studies need to be replicated before any broader conclusions can be drawn on the benefits of integration to service uptake and quality; moreover the studies lacked evidence on impact for health outcomes and service costs.

The Integra Initiative addresses these gaps and builds on this evidence from sub-Saharan Africa, as well as the expertise of its research partners. Since a partial evidence base exists for integration of HIV services (counseling, testing, risk assessment, care) into family planning and postpartum/postnatal services, these services have been selected as the focus of the Integra Initiative’s work which is in Eastern and Southern Africa – the regions with greatest need for HIV services.

### Study aims, hypotheses, objectives and indicators

The overarching aim of the Integra Initiative is to strengthen the evidence base on the impact of integrating family planning (FP), postpartum/postnatal care (PNC) and HIV services in sub-Saharan Africa. Specifically, in the study, we aim to assess the following three objectives:

1. To assess the extent to which different models of integrated service provision increase the range, uptake and quality of selected SRH and HIV services, and lead to a greater diversity in the profile of clients

2. To explore whether the provision of integrated HIV and SRH services leads to reductions in HIV risk-behavior; HIV related stigma and unintended pregnancies

3. To assess the efficiency of using different operational models for delivering integrated services in terms of: cost, utilization of existing infrastructure and human resources

### Definition and types of integration models

For the purposes of this study integration is defined as offering clients two or more services in the same visit. To better understand how services can be integrated in different countries, this study focuses on two key models of integration in Kenya and Swaziland. The first model focuses on integration of FP and HIV services (integrated FP model) and entails performing HIV testing, STI screening and management, cervical cancer screening, condom promotion within FP consultations, as well as active referral to antiretroviral (ART) units for HIV-positive clients (Figure 1). The FP model will be evaluated in Kenya only.

**Figure 1 F1:**
[figure not shown]
Package of integrated FP/HIV services.

The second model focuses on integration of PNC and HIV services (integrated PNC model) and will be implemented in both Kenya and Swaziland (Figure 2). The model focuses on the provision of PNC services to mother and baby, FP services, repeat HIV testing for mother, HIV testing for infant and referral to HIV services for HIV positive mothers and infants, as well as referrals for clients requiring additional services.

**Figure 2 F2:**
[figure not shown]
Package of integrated PNC/HIV services.

Two further models will be investigated as sub-studies to the main study which are not described in detail here. The first of these entails integrating FP and HIV/STI services (integrated SRH services model) in International Planned Parenthood Federation-Family Health Options Kenya (IPPF FHOK) and IPPF FLAS (Family Life Association of Swaziland) clinics in Kenya and Swaziland, respectively. This model focuses on the integration of the following services: FP, maternal and child health (MCH), HIV testing, HIV care, STI services, cervical cancer screening, and youth counselling. The second model focuses on the sexual and reproductive health needs of HIV-positive people in Swaziland and compares integrated SRH-HIV with stand-alone HIV services. Findings from these studies will be reported separately and more information on both sub-studies can be found on the Integra Initiative website: http://www.integrainitiative.org

### Description of intervention

Table 1 provides a summary of the programmatic components and related activities that will strengthen and maintain the provision of integrated FP/PNC and HIV services; introduce new services and develop and strengthen the linkages between the services that were not integrated at intervention facilities. Existing standard services will be compared with the strengthened integrated FP and PNC service models shown in Table 1.

**Table 1 T1:** Summary of the interventions in FP and PNC sites

**Intervention component**	**Model 1: FP-HIV Kenya**		**Model 2: PNC-HIV**
Pre-existing standard services	·Counselling & provision of FP methods		·**Timing:** Usually delivered on discharge if hospital delivery, with 6 week check:
	·Dual protection counselling		·**Content:**
	·Screening of STIs		·Immunisation
	·HIV prevention counselling		·Growth monitoring/child welfare
	·Counselling on sex & sexuality, childbearing and PMTCT.		·FP at six weeks postpartum (on request from mother)
	·Refer FP clients for STI treatment/ syndromic management		(NB: this is what should happen according to the guidelines but rarely does at facility level)
	·Refer FP clients for HIV counseling and testing		
	(NB: this is what should happen according to the guidelines but rarely does at facility level)		
Strengthened or additional services introduced	·All clients receive strengthened Standard FP services using the Balanced Counseling Strategy Plus. This includes:		·**Timing:** within 48 hours of delivery, plus 7 day, and 6 week visit at facility
	·Discussion of fertility desires,		·**Content:**
	·Offering a range of FP methods		·Mother and baby physical examination to detect danger signs, complications, anomalies
	·Ensuring suitability of FP methods		·Infant feeding counseling
	·Condom promotion/provision		·Postpartum FP counseling and provision
	·STI and HIV risk assessment		·Screening for cervical cancer (at 6 weeks)
	·Check client HIV status		·HIV counselling & testing (mother and baby)
	·HIV counseling and testing		·HIV treatment prophylaxis for
	·Screening for cancer of cervix (via /vili)		·mother and baby
	STI screening and management Arrange follow up appointments		Neonatal male circumcision (Swaziland only)
	**HIV negative clients** Health promotion Risk factor exposure Risk assessment (routine) for STI/HIV		
	**HIV positive clients** Counseling on HIV care and treatment available Manages clients with CD4 count >350 CTX prophylaxis Referred to lab/ART unit for blood tests		
Adaptation/ strengthening of protocols, guidelines and training materials	·Development, adaptation or updating of guidelines and protocols (where necessary) based on national guidelines and manuals		
	·Mentoring toolkit developed - includes trainers guide, log book for mentees, checklist		
	·Balanced Counseling Strategy Plus second edition adapted to include cervical cancer screening and postpartum car		
Staff training & management	·Development of an appropriate training and monitoring/ supervisory package which was grounded on the mentorship methodology and used the Balanced Counselling Strategy Plus (BCS+) toolkit		
	·Facilitative supervision comprising initially of bi-monthly and later quarterly visits by supervisory teams from the Ministries of Health and Population Council		
	·Training on technical skills for provision of long acting FP methods (IUDs and implants)		
	·Training on HIV counseling and testing, conseling on HIV services available, ARV refills, screening for STIs and syndromic management of STIs		
Organizational change and role clarification	·Organizational change of how services are provided (rooms identified for integrated services, partitions built to create more rooms and staff reallocated		
	·Role clarification with all staff - task oriented work changed to provision of services according to client need		
Equipment & supplies	·Ensuring availability of minimum levels of equipment and supplies (e.g., implant/IUD insertion kits, blood pressure machines and stethoscopes) required for providing integrated services		
Communication aids	·Improving the availability of information, education and communication/behavioral counseling and communication (IEC/BCC) materials. All IEC materials pertaining to FP/HIV and PNC/HIV reviewed and adapted to reflect provision of integrated services		
Referral systems	·Strengthened referral system between SRH clinics and ART centres (introduction of new referral forms (Kenya only)		
Data collection and management	·Strengthening data collection and recording systems through the development of data capture tools, (e.g., PNC registers and monthly data monitoring forms)		

In order to build consensus on the timing and composition of the package of services for both integration models, meetings were held with relevant stakeholders and the different levels of the Ministries of Health (MOH) in Kenya and Swaziland. Nine areas of intervention were identified (see list below) and to be carried out between August 2009 - December 2010 in both countries and for both models.

Summary of nine areas of intervention

1. Adaptation/strengthening of protocols, guidelines and training materials for HIV/SRH (where necessary)

2. Develop an appropriate training, mentoring and supervisory package for on job training

3. Improving provider capacity through mentorship (including technical skills for providing postpartum care for the mother and postnatal care for the infant, long term FP, HIV counseling and testing, HIV services, screening/management for STIs and cervical cancer)

4. Ensuring availability of minimum levels of equipment and supplies required for providing integrated services

5. Support supervision for integrated HIV/FP and HIV/PNC services

6. Organizational change to provide integrated services and role clarification for staff working at intervention sites

7. Improving the availability of IEC/BCC materials

8. Strengthened referral system between MCH-FP clinic and HIV units

9. Strengthening data collection and recording systems.

Guidelines and protocols on HIV, FP and PNC will be reviewed with MOH and stakeholders prior to developing or adapting an integrated package of care as well as the training approach. The training package will be grounded on the mentoring methodology, which is a creative and innovative strategy that prompts the sharing of information and skills among health workers (between a more experienced and less experienced health worker) in order to improve quality of care and/or introduce changes in service delivery. The mentoring approach aims to minimize disruption to ongoing service provision, i.e. one mentor based in a facility will impart her knowledge and skills to her colleagues. The training of mentors will be conducted over a 5-day period to build knowledge and skills in FP and /or PNC and HIV integration. Training job aids will also be reviewed and adapted including the Balanced Counselling Strategy Plus (BCS+) toolkit, a practical, interactive, and client-centered counselling approach that utilises an algorithm, counselling cards and brochures to facilitate FP consultations [23]. Following the introduction of the mentoring approach, supportive supervision will be conducted by the Integra Initiative and MOH officials to promote discussion and implementation of the activities including role clarification, organizational change, strengthened referral/linkages between SRH and HIV services and correct management of service statistics.

While all intervention activities will be uniformly delivered across the study sites, where necessary the activities will be customised to fit the aims and purpose of the two different models under evaluation. To ensure compliance or adherence with the intervention activities, supervision visits and facility meetings (with staff and management committees) will be conducted by teams comprising representatives from relevant departments at the MOHs in both countries and staff members from the Population Council.

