#### Sampling and indicators

Details on research methods are provided below; sampling strategy and sample size calculations for each method are summarised in Table 2.

The operational results (outcomes) and the main indicators that will be measured and analysed for each study objective are shown in Table 3.

**Table 3 T3:** Operational results and indicators to be used to compare results from the intervention and comparison health facilities

**Objective 1. Determine the benefits of different integrated models to increase range, uptake and quality of selected SRH and HIV services and to diversify the profile of clients.**		
**Results/Outcomes**	**Indicators**	**Data source**
Feasibility of linking services demonstrated	Number of internal and external referrals, Number of staff updated in HIV counseling and testing Number of staff updated in HIV BCC prevention, Facilities have adequate equipment and supplies	Service statistics Provider interviews Facility inventory
Provision of linked services to clients	Clients received CT in FP consultation, Clients referred for ART, Clients referred for other services, Number of referrals attended, Proportion of population demanding integrated services, Proportion of population accessing integrated services, Proportion of services users giving integration as a reason for choice of clinic	Client exit Provider interview Cohort Community Survey
Increased % of eligible HIV+ women starting to use ART	Proportion of women reaching referral site clients know their CD4 counts	Service statistics Cohort
Increased uptake of range of SRH services including integrated CT, FP, PNC and STI screening services	% FP clients accessing more than one service Proportion of population accessing more than one service at last FP or PNC visit	Service statistics Exit /Cohort Community Survey
Increased quality of a range of SRH services	% clients receiving minimum level of quality services	Client – provider interaction, exit interview
Increase in number and diversity of clients	% men and women using component services Proportion of clients using component services by age, SES and gender	Community Service Statistics Client exit /CPI
Increased numbers of clients screened/managed for STIs	% FP clients accessing separate/integrated services	Service statistics Client Flow Cohort
Increased in new and repeat FP clients testing for HIV		Service statistics Cohort

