This will involve collection of routine program monitoring data on utilization of family planning, postpartum/postnatal and HIV services. Forms will be used to extract client register data on a monthly basis for further analysis. Analysis of routine program data will contribute to answering the following questions: 1) what is the change in client profile pre- and post-integration (for instance, in terms of age, and sex)?, 2) does the rate of new clients accessing the services increase post-integration?, and 3) what are the changes in range of service uptake and client-profile pre- and post-integration across a range of SRH/HIV services.

c) Costing of service delivery across the different models

In each of the study facilities, the costs of delivering integrated SRH-HIV services will be measured both at baseline and endline, and the potential for efficiency gains will be assessed. Where feasible these cost data will be combined with an effectiveness analysis (with client and population level data) to estimate the cost-effectiveness of integrated services.

A periodic activity review (PAR) tool will be used to provide a mapping of how resources are combined to produce integrated HIV and SRH services in each study facility at baseline. The tool will include questions on facility characteristics, staffing types and levels, scope and number of services offered, clinical practice, descriptions of client flow, and overall description of how integration of services works from the provider’s perspective. Building on the PAR, the unit cost study will estimate the quantity and value of resources that are used to implement activities at facility level. Costing tools will be developed from the first round of data from the PAR, but will generally be based on UNAIDS costing guidelines: *The Costing Guidelines for HIV Prevention Strategies*[33].

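### Better record-keeping is part of the intervention package, and service statistics are one outcome source for six Objective 1 results, so improved recording can look like increased uptake, mainly in counts

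*Protocol article*

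**What the plan says.** In the protocol article, Description of intervention, the last component of Table 1 is "Strengthening data collection and recording systems through the development of data capture tools, (e.g., PNC registers and monthly data monitoring forms". The referral component includes "introduction of new referral forms (Kenya only". The ninth of the nine listed intervention areas is "Strengthening data collection and recording systems", and supportive supervision is meant to promote "strengthened referral/linkages between SRH and HIV services and correct management of service statistics". The contrast is set out in the same section: "Existing standard services will be compared with the strengthened integrated FP and PNC service models shown in Table 1".

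On the outcome side, Table 3 is captioned "Operational results and indicators to be used to compare results from the intervention and comparison health facilities". Under Objective 1 it names service statistics as a data source in six rows. Under Prospective routine monitoring, "Forms will be used to extract client register data on a monthly basis for further analysis". Those extracts are to show whether client profile, the rate of new clients and the range of services used change from before to after integration.

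The article describes no check on how complete the registers are. The one measurement bias it acknowledges is the effect of observers on consultations.

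**The concern.** The package changes the instrument that produces some of the outcome data, and it does so as the intervention starts. A controlled before-and-after design removes recording error that is stable over time or shared by both arms. It does not remove error that shifts in the intervention facilities when the package arrives, because that shift enters the effect estimate directly. Registers alone cannot then separate more clients served from more clients written down. What is at stake is the reading of register-based trends under Objective 1, chiefly the number of referrals, the number of clients and the rate of new clients.

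**Working it through.** No figure in the article is in dispute, so there is none to reproduce. The check sets the passages side by side and then illustrates the size.

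**1. Which results draw on service statistics, and what else is listed (Table 3, Objective 1)**

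| Result | Other sources listed |
|---|---|
| Feasibility of linkage, including number of referrals | Provider interviews, facility inventory |
| ART start among eligible HIV-positive women | Cohort |
| Uptake of the range of services | Exit interviews/cohort, community survey |
| Number and diversity of clients | Community survey, exit interviews/observations |
| STI screening and management | Client flow, cohort |
| HIV testing in new and repeat FP clients | Cohort |

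No row depends on service statistics alone, and no Objective 2 row uses them.

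**2. How far the other sources can stand in**

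- Neither provider interviews nor the facility inventory is described as counting referrals.
- The cohort is recruited after the post-intervention facility assessment, so it has no pre-intervention measure. Its FP arm takes revisit clients only, so it has no new FP clients.
- Exit interviews use a small set number of clients per facility (18 in the Kenya FP entry of Table 2). They inform proportions, not volumes.
- Client flow records all consenting MCH clients over five days, with services received and referrals made. It belongs to the facility assessments, which include a pre-intervention round, but it is listed in only one of the six rows.

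**3. Size for a count**

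Inputs, all assumed: true volume T is unchanged in both arms; completeness is c0 everywhere before and in comparison sites after; completeness is c1 in intervention sites after.

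Recorded count = T × completeness, so

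spurious ratio = (T·c1 / T·c0) ÷ (T·c0 / T·c0) = c1 / c0.

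- 90% to 95%: 0.95/0.90 = 1.06
- 80% to 95%: 0.95/0.80 = 1.19
- 70% to 95%: 0.95/0.70 = 1.36
- 60% to 95%: 0.95/0.60 = 1.58

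For example, at 100 true clients a month and a rise from 80% to 95%, intervention records go from 80 to 95 while comparison records stay at 80. The difference-in-differences is 15 clients a month with no change in use.

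**4. Size and direction for a proportion**

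With numerator completeness cN and denominator completeness cD,

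spurious ratio = (cN1/cN0) ÷ (cD1/cD0).

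- Both rise from 80% to 95%: 1.19 ÷ 1.19 = 1.00, so the artefact cancels.
- Only the numerator rises from 80% to 95%: 1.19.
- Only the denominator rises from 80% to 95%: 0.80/0.95 = 0.84. This could happen to the proportion reaching the referral site if new forms capture more of the referrals made.

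**The case against.** The strongest reply is that the article already leans on other instruments. Data management and analysis names the datasets for multivariable modelling as observations and exit interviews, cohort, client flow, community survey and periodic activity review; registers are not among them. The design section also promises triangulation, and it places service utilisation under adequacy, meaning whether expected changes occurred in intervention facilities. The routine monitoring questions are phrased as before and after, not as arm against arm. All of this stands, and it narrows the point. It does not remove it. Triangulation comes with no rule for a recording change or for which source prevails, the Table 3 caption covers the service-statistics rows, and a before-and-after register trend is exposed to the same artefact.

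A second reply is that the article never says comparison sites are denied the new registers, and it speaks of uniform delivery of activities across study sites. That is fair: delivery to intervention facilities only is the natural reading of a contrast between standard services and the Table 1 package, but it is not stated outright. The register named is the PNC register, given as an example; no change to an FP register is named.

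A reader might go further and infer that registers are the sole basis for the uptake outcomes, that the bias must favour the intervention, or that the main outcomes are compromised. The documents support none of these. Every affected row has another source, proportions can stay level or fall, and condom use and unintended pregnancy come from cohort interviews.

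**Conclusion.** The point holds as a limited one. Where service statistics feed an Objective 1 result, a rise that coincides with the package can be partly or wholly a recording effect, and the before-and-after contrast between arms does not remove it. Counts are the main exposure. For proportions the sign is uncertain. Objective 2, the cohort sample-size outcomes and the integration index (built from client flow and costing tools) are not affected.

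The size cannot be fixed from the article. The range of 1.06 to 1.58 rests on assumed completeness, on unchanged true volume, and on recording that improves in intervention sites only. If comparison sites received the same tools at the same time, the between-arm part would shrink or vanish, though the before-and-after trend would still be exposed.

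**What to change.** For the six Table 3 rows that list service statistics, state that the pre/post intervention-versus-comparison contrast comes from instruments applied identically in both arms: client flow for volumes and referrals, exit interviews for proportions among clients. Use the cohort only for post-intervention comparison between arms. Where neither client flow nor exit interviews captures an indicator, say that no unaffected pre/post contrast is available. Label service statistics as supportive.

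For each facility and round, count register entries for the five client flow days, for the services that client flow covers, and divide by the client flow count. Report this completeness by arm and period. Correct register trends with it, or caveat them where the ratio moves.

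The cost is a change of analysis wording and a small extra register count on days already being observed. The downsides are that five days per round give noisier estimates than monthly counts, and that client flow forms are filled in by providers, so client flow is not wholly independent of their recording habits.
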